### Sample size

Power analyses were generated using the two-group repeated proportions module in PASS 2020 [68] to compute minimum detectable effect sizes for the proposed primary analysis. The study will include 350 participants equally assigned to the intervention and control groups. We assume that as much as 10% of the sample may drop-out at each follow-up; however, we anticipate better retention due to SSP staff engagement in the study [69]. The expected sample sizes at the four follow-ups are thus 315, 284, 255, and 230. Using these sample sizes and assuming α = 0.025, power = 0.80, and that the proportion with PrEP or MOUD engagement will be 30% of the control arm, we computed the minimum detectable odds ratio (OR) 1.56 and absolute proportion difference (pdiff) of 0.101, assuming that all post-intervention time points are part of the contrast. We varied the within-subject correlation ρ from 0.10 to 0.80. Power for a binomial is lowest when the base-rate (control group) probability (P_0_) is near 50%.

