##### *Hypothesis 1*

*C-THR* will be superior to non-SSP clinic referral and patient navigation in promoting engagement in HIV prevention as measured by the proportion of participants taking PrEP and/or MOUD across follow-up at 3, 6, 9 and 12 months post-randomization.

### Primary inferential analyses to address primary hypothesis of objective 1

We hypothesize that, for those randomized to the *C-THR* arm, the odds of our two co-primary outcomes, engagement in PrEP and engagement in MOUD, will be higher than for those randomized to the non-SSP clinic patient navigation, control arm (Hypothesis 1). Generalized estimating equations (GEE) [92] will be used to perform the proposed primary analysis, which is a planned time-averaged comparison of all post-baseline measurements of the each of these outcomes—PrEP: DBS evidence of tenofovir or cabotegravir injection in the previous 8 weeks by electronic health record abstraction; MOUD: UDS with norbuprenorphine or methadone/EDDP; or naltrexone or buprenorphine injection in previous 4 weeks by electronic health record abstraction—across the *C-THR* and control groups to test primary Hypothesis 1. Alpha will be set at 0.025 for this planned comparison to control the Type-1 error across these two co-primary outcomes. In each model, recruitment site (fixed site vs. mobile site) and OUD diagnosis (yes vs. no) will be included in these analyses as required by the stratified randomized design to obtain unbiased results. If the overall test of the intervention is statistically significant, individual contrasts for differences between the conditions at each of the times of follow-up will be performed.

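### The fixed 0.025 for each co-primary outcome is valid, but a Holm step-down at the same 5% family-wise error would be a cheap, optional gain in power for the second outcome

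*Protocol article*

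**What the plan says.** Under Hypothesis 1 and the primary inferential analyses for objective 1, the protocol article expects that "the odds of our two co-primary outcomes, engagement in PrEP and engagement in MOUD, will be higher" in the C-THR arm. Each outcome gets its own GEE model with a time-averaged comparison of the arms. The level is stated once for both: "Alpha will be set at 0.025 for this planned comparison to control the Type-1 error across these two co-primary outcomes". Contrasts at single follow-up times are run only if the overall test is significant.

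The Sample size section uses the same level: "assuming α = 0.025, power = 0.80, and that the proportion with PrEP or MOUD engagement will be 30% of the control arm". From this, "we computed the minimum detectable odds ratio (OR) 1.56 and absolute proportion difference (pdiff) of 0.101".

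No step-down, fallback or recycling of alpha appears anywhere in the article. It gives neither the correlation between the two outcomes nor the power to show both. It does not say whether the tests are one- or two-sided.

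**The concern.** The rule is a plain equal Bonferroni split: each outcome faces 0.025 whatever happens to the other. Dividing alpha implies that a result on either outcome counts, because no division would be needed if both were required. In that setting Holm serves the same purpose with more rejections. It tests the smaller p-value at 0.025 and, if that passes, the larger at 0.05.

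What is at stake is a second claim with a p-value between 0.025 and 0.05. With p = 0.001 for PrEP and p = 0.03 for MOUD, the plan declares MOUD negative and skips its time-point contrasts. Holm would allow both claims within the same 5% limit. The trial asks whether one care model raises uptake of two services, so the second claim matters to readers.

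**Working it through.** **Inputs from the Sample size section.** Control proportion 30%, alpha 0.025, power 0.80; 350 randomised 1:1; "The expected sample sizes at the four follow-ups are thus 315, 284, 255, and 230"; "We varied the within-subject correlation ρ from 0.10 to 0.80".

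**Assumptions.** Two-sided tests, since that reproduces the stated odds ratio at the lowest within-subject correlation. A correlation r between the PrEP and MOUD test statistics, for which the document gives no value, so a range is shown.

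**1. The plan's own figure.** The four sample sizes imply 31, 29, 25 and 230 people with 1, 2, 3 and 4 visits. A person with m visits contributes m / (1 + (m − 1)ρ) effective observations. At ρ = 0.10:

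31 + 29 × 2/1.1 + 25 × 3/1.2 + 230 × 4/1.3 = 31 + 52.7 + 62.5 + 707.7 = 854.

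A two-proportion test with 427 per arm, a control rate of 0.30, two-sided 0.025 and 80% power detects a difference of 0.101, an odds ratio of 1.56. The stated figures reproduce.

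**2. Power at each level.** Critical values are 2.241 (two-sided 0.025) and 1.960 (two-sided 0.05). For 80% power at 0.025 the mean of the test statistic is 2.241 + 0.842 = 3.083. Power at 0.05 is then Φ(3.083 − 1.960) = 0.869.

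**3. Holm with r = 0.**
- Each outcome: 0.80 + 0.80 × (0.869 − 0.80) = 0.855.
- Both: 2 × 0.80 × 0.869 − 0.80² = 0.751, against 0.80² = 0.640 for the fixed split.
- At least one: 1 − 0.20² = 0.960 under either rule.

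**4. Other correlations (bivariate normal), 80% power for each outcome under the fixed split.**

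| r | Each, Holm | Gain (points) | Both, fixed | Both, Holm | Gain (points) |
|---|---|---|---|---|---|
| 0 | 85.5% | 5.5 | 64.0% | 75.1% | 11.1 |
| 0.3 | 85.0% | 5.0 | 66.6% | 76.6% | 10.0 |
| 0.5 | 84.6% | 4.6 | 68.7% | 77.8% | 9.1 |
| 0.7 | 84.1% | 4.1 | 71.3% | 79.4% | 8.1 |

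**5. Unequal power, 80% and 30%, r = 0.** The weaker statistic has mean 2.241 − 0.524 = 1.717, so its power at 0.05 is Φ(1.717 − 1.960) = 0.404. Gains:
- stronger outcome: 0.30 × (0.869 − 0.80) = 2.1 points;
- weaker outcome: 0.80 × (0.404 − 0.30) = 8.3 points.

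**6. Power below plan.** At an odds ratio of 1.56, power per outcome is 71.5%, 52.4% and 40.8% for ρ = 0.2, 0.5 and 0.8. For r between 0 and 0.3, Holm then adds about 4.5 to 6.2 points per outcome and 9 to 12.5 points for both.

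**7. Error rates.**
- Both nulls true, r = 0: 1 − 0.975² = 4.9% under either rule. Simulation gives 4.8% at r = 0.3 and 4.7% at r = 0.5.
- One null true, the other outcome at 80% power, r = 0: a false claim has probability 2.5% under the fixed split and 0.025 + 0.80 × 0.025 = 4.5% under Holm (simulated 4.4% at r = 0.3 and 4.3% at r = 0.5). If the other outcome is certain to pass, it reaches the ceiling of 5%.
- In that case the outcome with a true effect gains only 0.025 × (0.869 − 0.80) = 0.2 points.

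**The case against.** The strongest reply is that the plan states nothing wrongly. An equal split is a standard, pre-specified method that does what the protocol says it is for, and design and analysis use the same level. That stands.

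A reader might go further and infer that the split gives up power for nothing, or that Holm costs nothing in error. The figures do not support this. When C-THR truly moves only one outcome, the chance of a false claim on the other rises from 2.5% to about 4.5%, while the real effect gains about 0.2 points. The split also lets each outcome be read alone, and 97.5% intervals match its decisions. With Holm they will not always match the second decision.

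A reader might also take the gain as a fixed 5 points per outcome and 10 to 11 for both. That needs 80% power on both outcomes and a between-test correlation of about 0 to 0.3, neither of which the document establishes. The 80% holds by construction at a minimum detectable effect computed from one 30% control rate. The Background reports PrEP uptake and persistence of 0–3% among people who inject drugs, and randomisation is stratified by OUD because not everyone has that diagnosis. Equal power is therefore doubtful.

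Finally, Hypothesis 1 is worded so that either service suffices, and the document never powers for showing both. The chance of at least one positive result is the same under both rules.

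What remains is narrower. The protocol fixes the rule itself, so this is not a detail left to an unseen analysis plan. Under the stated aim of controlling error across two outcomes, Holm never rejects less and sometimes rejects more.

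**Conclusion.** The fixed 0.025 is valid but less efficient than Holm at the same 5% family-wise limit. This is an optional, cheap improvement and not an error. With 80% power per outcome at two-sided 0.025, the gain is about 4 to 6 points per outcome and 8 to 11 points for both, for correlations from 0.7 down to 0. Equal power, the correlation and the two-sided tests are assumptions. With powers of 80% and 30% and zero correlation, the gains are about 2 and 8 points; with one true effect, almost none. The minimum detectable odds ratio of 1.56 is unchanged, because Holm's first step stays at 0.025. The document does not support a reading that the trial's error control or sample size is faulty on this account.

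**What to change.** In the primary inferential analyses for objective 1, replace the fixed level with: test the smaller of the two p-values at 0.025; if significant, test the larger at 0.05; otherwise stop. Let the same decision trigger the time-point contrasts for each outcome. Leave the Sample size section at 0.025, which is Holm's first step. Say which level the conditional-power calculation under Interim analyses uses.

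Settle this before any outcome data by arm are seen, including a futility look, which uses the observed effect. The article commits only to confirming the analysis plan before data lock; in an open-label trial that is too late to relax a published criterion.

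The cost is one sentence plus the contrast rule, and IRB approval if handled as a protocol amendment. No participants or data are added. The report should say that 97.5% intervals may not mirror the second decision, and that the false-positive chance on a single null outcome rises from 2.5% to about 4.5%, at most 5%.

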Number of harms	Count of (1) emergency department visit or hospitalization for injection-related infection or overdose; (2) incident HIV infection; (3) incident HCV infection; or (4) death from overdose	(1) Electronic health record abstraction; (2, 3) IDEA test results (4) electronic health record abstraction or medical examiner database

Secondary analyses will evaluate positive health behaviors by counts per person per study arm. PrEP adherence will be defined as taking PrEP at least four times per week for men and at least 6 times per week for women as confirmed by TFV-DP levels on DBS. HCV treatment engagement will be defined as receipt of a prescription for DAA. HCV cure will be defined as sustained virologic response at least 12 weeks after completing DAA (SVR 12) and treatment of STIs is defined as receipt of the appropriate antibiotic treatment after diagnosis. Secondary outcomes will also evaluate negative health outcomes or harms by counts per person per study group. Emergency department visits or hospitalizations will be confirmed by participants’ consent for records release and abstraction from Miami area hospitals which have integrated electronic health records. Incident HIV and HCV infections (or reinfections) will be confirmed by positive 4th generation HIV antigen/antibody test and detected HCV RNA, respectively. Death from overdose will be confirmed by hospital record, Miami-Dade County Medical Examiner database search or direct inquiry with the medical examiner. In addition to counts, time to secondary outcomes, both positive and negative, will be compared by study arm.

For objective 2, the primary health economic outcomes will be: (1) implementation and ongoing management costs of the two healthcare models, and (2) short-term cost-effectiveness from the perspectives of the healthcare sector and society. The primary economic outcome will be the incremental cost-effectiveness ratio (ICER) from the healthcare sector and modified societal perspectives. The measure of effectiveness will be quality-adjusted life years (QALYs) and incident HIV infections averted.

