Though GEE estimates are consistent even if the correlation structure is misspecified, GEE's statistical efficiency improves as the working correlation structure more closely approximates the actual correlation structure [92], so various correlation structures suitable for the study's design will be considered (e.g., exchangeable, autocorrelated, *m*-dependent, unstructured) [93]. The QIC statistic will be used to select the final correlation structure [94]. Recruitment site (fixed site vs. mobile site) and OUD diagnosis (yes vs. no) will be included in all models as required by the stratified randomized design to obtain unbiased results [95]. Robust standard errors will be used to obtain correct inferences even if the chosen correlation structure remains slightly mis-specified. All analyses will include outlier and influential case screening via computation of GEE-based residual analysis, including leverage, DFBeta, and Cook’s D statistics [96]. If outliers are found, results will be reported with and without outliers included.

### Data analysis plan and statistical procedures to address secondary hypotheses of objective 1

We have proposed several secondary hypotheses related to the *C-THR* intervention. The secondary analyses will use exactly the same preliminary analysis and missing data strategy as Hypothesis 1. In secondary analyses, we will examine the distributions of syringe coverage, PrEP adherence, HCV treatment engagement, HCV cure, STI treatment uptake, and number of injection related harms and assess time to first injection-related harm between the intervention and control groups. GEE [92] will be used to perform the proposed secondary analysis, which is a planned time-averaged comparison of all post-baseline measurements of the each of these outcomes. Statistical procedures for these secondary hypotheses will follow the same strategy used for the primary hypothesis. The alpha will be set at 0.05 for each these secondary hypotheses. In each model, recruitment site (fixed site vs. mobile site) and OUD diagnosis (yes vs. no) will be included in these analyses as required by the stratified randomized design to obtain unbiased results. To maximize rigor, appropriate diagnostics including outlier and influential case screening will be examined for each model. If outliers are found, results will be reported with and without outliers included.

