### Sex as a biological variable

We will examine the primary hypothesis and secondary hypotheses with respect to difference by sex. In particular, the primary analysis method will be used and a sex by treatment interaction in the time-averaged odds of engagement in HIV prevention will be added to the model to test whether there are differential treatment effects by sex. With the expected 120 or 1/3 of the sample women, there is reasonable power to uncover a difference.

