### Mediation analyses

The impact of *C-THR* on our hypothesized outcomes will be mediated through reductions in stigma. To maximize rigor, these analyses will not be performed with classical multiple regression-based mediation techniques such as the Baron and Kenny causal steps approach [97]. Instead, mediation analyses will be conducted using structural equation modeling (SEM) and bootstrapped tests of significance of the product of coefficients (a*b, where a is the path coefficient from the intervention to mediator, and b is the path coefficient from mediator to outcome). We will use M*plus* [91] to perform mediation analyses because it unites SEM with causal inference-based mediation methods in the same analysis platform [98]. Alpha will be set at 0.05 for all hypothesis tests in these exploratory analyses.

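### Seven secondary hypotheses are each tested at a full 0.05 with no order, adjustment or supportive label, while error control covers only the two co-primaries

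*Protocol article*

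**What the plan says.** All references are to the protocol article.

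- **Co-primaries** (Primary inferential analyses to address primary hypothesis of objective 1): "Alpha will be set at 0.025 for this planned comparison to control the Type-1 error across these two co-primary outcomes". The only gate in the analysis text is in the same section and concerns visit-wise comparisons of the same outcome: "If the overall test of the intervention is statistically significant, individual contrasts for differences between the conditions" at each follow-up time come next.
- **Secondaries** (Data analysis plan and statistical procedures to address secondary hypotheses of objective 1): six outcomes are listed in the words "we will examine the distributions of syringe coverage, PrEP adherence, HCV treatment engagement, HCV cure, STI treatment uptake, and number of injection related harms". The seventh is how long participants go before their first harm, compared between arms by logrank test. That makes seven. On the level: "The alpha will be set at 0.05 for each these secondary hypotheses".
- **Further secondary comparisons** (Outcomes, text after Table 1): "In addition to counts, time to secondary outcomes, both positive and negative, will be compared by study arm". The number of these is not given.
- **Sex** (Sex as a biological variable): "We will examine the primary hypothesis and secondary hypotheses with respect to difference by sex". The interaction model is spelled out only for engagement, with no alpha and no status.
- **Exploratory label**: it appears only under Mediation analyses: "Alpha will be set at 0.05 for all hypothesis tests in these exploratory analyses".

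**The concern.** The article treats multiplicity as something to control when there are two tests, then gives seven further tests the full 0.05 each. It calls them hypotheses, sets a significance level for each, and does not say what a significant result would license. Because it uses the exploratory label for mediation and not here, a reader can take the secondaries as tests that stand on their own.

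Two features of this trial sharpen the point.

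- **PrEP adherence against PrEP engagement.** Adherence is a TFV-DP threshold on dried blood spot, the assay that also feeds the PrEP co-primary (which additionally counts cabotegravir injections). If both gave p = 0.04, engagement would miss its 0.025 level while adherence would meet its 0.05 level.
- **Harms.** The number of harms and the time to first harm use the same four-part event definition, are tested separately, and neither is named as the lead.

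The trial is open-label, and its results are intended for policymakers and national organisations. What is at stake is how an isolated secondary result would be read, above all if the co-primaries were not significant.

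**Working it through.** **Inputs from the article.** Two co-primaries at 0.025 each; seven secondaries at 0.05 each.

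**Assumptions, because the article is silent.** Tests are two-sided; all seven null hypotheses are true; the correlation between test statistics is unknown and is varied.

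**1. The plan's own control, reproduced.** The co-primary levels add to 0.025 + 0.025 = 0.05. Under independence the family-wise error is 1 − 0.975² = 0.0494. The stated control holds.

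**2. Seven secondaries, independent.** 1 − 0.95⁷ = 1 − 0.698 = 0.302.

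**3. Seven secondaries, common correlation ρ.** With c = 1.96 and X standard normal,

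FWER(ρ) = 1 − E{[Φ((c − √ρ·X)/√(1−ρ)) − Φ((−c − √ρ·X)/√(1−ρ))]⁷}.

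For results favouring C-THR only, the second Φ term is dropped. At ρ = 0 this is 1 − 0.975⁷ = 1 − 0.838 = 0.162.

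| Assumed ρ | Any false positive, either direction | False positive favouring C-THR |
|---|---|---|
| 0 | 30.2% | 16.2% |
| 0.2 | 28.7% | 14.7% |
| 0.5 | 23.0% | 11.5% |
| 0.8 | 14.9% | 7.4% |

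**4. A less uniform structure.** Suppose only the two natural pairs (HCV treatment with HCV cure; harm count with time to first harm) are strongly correlated, at 0.5 to 0.9, and all other correlations are 0 to 0.3. Simulation then gives 24% to 29% in either direction.

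**5. What is not counted.** The extra time-to-event comparisons would raise these figures. Their number is not stated, so no figure is put on them. The sex interactions are not included either.

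**6. Holm on the co-primaries.** Holm tests the smaller p at 0.025 and, if that succeeds, the other at 0.05. It rejects whatever the fixed split rejects, so it cannot lose power, and it keeps the family-wise level at 0.05.

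- Let each outcome have 80% power at two-sided 0.025. The standardised effect is 2.241 + 0.842 = 3.083, and power at 0.05 is Φ(3.083 − 1.960) = 0.869.
- Fixed split, independent outcomes: power to win both is 0.80² = 0.640.
- Holm: both p-values below 0.05, less the case where both lie between 0.025 and 0.05, which is 0.869² − 0.069² = 0.756 − 0.005 = 0.751.
- At correlation 0.5 between the two statistics, the gain is from 0.687 to 0.778.

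**The case against.** The strongest reply is that nothing stated is wrong. The article confines its error control to the two co-primaries, only Hypothesis 1 carries the superiority claim, and the word secondary already ranks the other outcomes below it. Unadjusted secondary tests are common, interpretation is often left to the analysis plan, and the section on blinding says the final plan will be confirmed before data lock. Much of this stands, and it is why the point is modest. It does not remove the point, because the 0.05 per hypothesis is fixed in this document and an analysis plan that follows it inherits the rule.

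A reader might be tempted by four stronger readings that the document does not support.

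- **A single headline rate of about 23%.** That needs a common correlation of 0.5 among all seven statistics, which the article does not give.
- **A false headline for C-THR in roughly one trial in four.** Figures of that size count false results in both directions. At correlation 0.5, the rate favouring C-THR is 11.5%.
- **That the plan allows an efficacy claim on a secondary.** No passage says so; the gap is that none says otherwise.
- **That the secondaries should open only if both co-primaries succeed.** The split at 0.025 lets either co-primary succeed alone, so this would add a success rule the trial lacks. Even with Holm and 80% power for each co-primary, the secondary family would stay closed in 1 − 0.778 = 22% to 1 − 0.751 = 25% of trials, and however small a secondary p-value was, it would not count.

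It is also fair that the two harm analyses, being closely related, add less error than two independent tests would, and that a sex interaction tests effect modification, not efficacy.

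**Conclusion.** The point holds in a limited form. Seven named secondary hypotheses are each tested at 0.05 with no order, adjustment or supportive label. If all seven nulls are true and tests are two-sided, at least one false positive is expected in 30% of trials under independence and in 15% to 29% for assumed common correlations of 0.8 down to 0.2. For false results favouring C-THR only, the figures are about 16% under independence and 11.5% at correlation 0.5. If some secondaries are truly affected, fewer nulls remain and the rates fall.

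The co-primary inference and the sample size are untouched. Whether to adjust secondaries formally is a trade-off for the investigators; stating their status is not, because it costs almost nothing.

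**What to change.** **(a) Secondary outcomes.** Replace the alpha sentence in the secondary-analysis section with wording such as: *Secondary outcomes, their time-to-event versions and sex interactions are supportive; they are reported with estimates and unadjusted 95% CIs, and no efficacy claim rests on them.* Name either the harm count or the time to first harm as the lead harm analysis. This needs no data, participants or procedures. The cost is that no secondary can be presented as confirmatory, whatever its p-value.

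**(b) Co-primaries, a separate and optional gain.** In the primary-analysis section, replace the fixed 0.025 for each outcome with Holm: the smaller p at 0.025 and, if that succeeds, the other at 0.05. The family-wise level stays at 0.05, either outcome can still succeed alone, and no power is lost. The sample-size calculation at 0.025 remains valid and becomes slightly conservative. The cost is a wording change made before data lock.
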